#### Statistical analyses

Multilevel logistic regression analyses will be used (MLwiN) to examine differences between the three study groups on smoking status and cognitions in favour of (non-)smoking. Mediation and moderation analyses will be performed to identify cognitive factors as mediators of the intervention effect and to explore differential effects in sub-groups, for example, based on demographic characteristics. Data of process evaluation interviews held after 12 and 24 months among pupils will be analysed using Nvivo.

#### Ethical approval

This study is approved by the Medical Ethics Committee of the Atrium-Orbis-Zuyd Hospital (NL32093.096.11/MEC 11-T-25) and registered in the Dutch Trial Register (NTR3116).

## Discussion

In this paper the design of the intervention and evaluation protocol of the ‘Fun without Smokes’ programme has been presented.

The present study aims to develop a computer-tailored smoking prevention programme for primary school children, in which they will be provided with the necessary attitudes, knowledge, skills and plans to refuse cigarettes when they make the transition from primary to secondary school. The programme is an adaptation and translation of an existing computer-tailored intervention that was previously print-delivered. The content of the computer-tailored feedback was similar to the original print-delivered version, but the messages are much shorter to comply with the requirements that messages through the Internet should not be too long. The time interval of sending the feedback letters was made shorter (one day as opposed to two weeks in the print-delivered version), since this was preferred by the pupils. Furthermore, the web-based delivery allowed for the creation of a more comprehensive website where children could find more information about (non-)smoking, games and additional movies concerning (non-)smoking. This website was used to facilitate multiple exposure to non-smoking information and to be able to provide multiple feedback.

The structural approach - involvement of pupils, using a medium preferred by pupils and pre-testing of the programme - is a good basis for an effective intervention and increases the likelihood that the web-based approach is attractive to pupils. Two versions of the intervention will be tested in a three-group cluster randomised controlled trial. It is hypothesised that pupils in the intervention conditions will be less likely to start (experimenting with) smoking compared with the control condition, and that the smoking rates will be lower in the intervention + prompt condition than the intervention condition.

### Strengths and limitations

Previous in-school smoking prevention programmes required much investment in time from the participating (primary) schools [45], leading to frustration and higher drop-out rates of participants or schools. The ‘Fun without Smokes’ programme is a web-based intervention, which requires only a very limited input and time from teachers, and thus meets the needs of schools to lower workloads involved in implementing smoking prevention programmes. A second strength is the design of the effectiveness study, since it assesses effects not only immediately, but also after 12 and 24 months. This allows testing both the short- and long-term effects of the ‘Fun without Smokes’ programme.

A possible limitation of the study is that smoking behaviour and other factors related to smoking are based on self-reports of youngsters, which might lead to measurement errors (i.e. social desirable answers). To avoid social desirable answers, we will guarantee full confidentiality to our participants. The validity of adolescent self-reported smoking has been shown to be high in accordance with biological indicators when measurement assures confidentiality [46]. Approximately 60% is expected to drop-out in the final measurement, since pupils are not connected to their primary school anymore. This drop-out percentage is taken into account in the sample size calculation. The large sample size will guarantee enough power for the evaluation study.

If the programme is proven to be effective, it will be a valuable tool for smoking prevention that can readily be implemented in primary schools in the Netherlands. This study will, furthermore, provide valuable information about the usability and additional effects of SMS and e-mail reminders in combination with a computer-tailored feedback programme.

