**Figure 1 F1:**
[figure not shown]
Design of ‘Fun without Smokes’.

All participants will be invited to complete the full assessment questionnaire again 12 and 24 months after the baseline questionnaire is completed, to receive repeated feedback letters about changes in smoking status or key determinants (e.g. attitude, social influences and self-efficacy expectations). However, the tailored advice will take into account the answers of the pupils of the previous measurements.

To increase the probability that the intervention will be attractive, 87 pupils from grade 7 and 8 (10-12 year olds) were involved in the development process. Group interviews were performed to select the name, colour scheme and design for the intervention and website. After developing several lay-outs, websites and logos these were presented to children and they were asked to choose their favourite name. ‘Fun without Smokes’ came out as the most popular. Additionally, short animations were developed to make completion of the questionnaire more attractive. In those animations the consequences of smoking were depicted by animals. Children appreciated these animations.

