### Evaluation design

#### Objectives and design

Both versions of the ‘Fun without Smokes’ programme (intervention and intervention + prompt condition) will be evaluated in a cluster randomised controlled trial with a no information control condition. The aim is to test the effectiveness of the programme on prevention of smoking initiation and on cognitions in favour of non-smoking at 12 and 24 months post baseline, as well as the additional effect of prompts on the usage of the website and on the outcome measures. Schools were the units of randomisation.

Assessment of smoking behaviour and smoking related cognitions will be at baseline and 12 and 24 months later, by means of web-based questionnaires.

Ever smoking is chosen as the primary outcome measure, because prevalence rates of monthly smoking are generally low at the age of 13 (8% at this age in 2010 [4]). Additionally, the level of utilisation of the website will be a primary outcome measure. This outcome will be operationalized as the number of visits to the ‘Fun without Smokes’ website and is expected to be significantly higher in the intervention + prompt condition compared with the intervention condition. Secondary outcome measures are attitudes, social influences, self-efficacy, intention to smoke and monthly smoking.

The hypotheses for this study are:

1. Providing children with computer-tailored feedback about non-smoking will prevent smoking initiation;

2. Children receiving computer-tailored feedback about non-smoking will have stronger cognitions in favour of non-smoking;

3. Computer-tailored feedback about non-smoking and prompting children through e-mail and SMS to revisit the website will result in a stronger effect on the prevention of smoking initiation (and on cognitions in favour of non-smoking) than tailored feedback only;

4. Children receiving computer-tailored feedback, SMS and e-mails will visit the website more often than children receiving computer-tailored feedback only.

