#### Procedure

The baseline questionnaire (which is also the screening instrument for the tailored feedback messages) was completed during school hours under the supervision of a teacher, who also distributed to all participating children their personal log-in details in sealed envelopes. Non-participating children were instructed by the teacher to do something else. The same procedure will be employed for the one year follow-up assessment. The two year follow-up questionnaire will have to be completed at home, since by that time the children will have left primary school. For the two year follow-up the participants will be contacted via mail and e-mail inviting them to complete the web-based questionnaire.

After completion of the baseline and 12 months questionnaire, the children in the intervention groups will receive short summaries of the tailored feedback on their computer screen. Extended tailored advice will be sent one hour after completion of the web-based questionnaire as pdf attachment to the respondents e-mail address and will be posted on the website. In the next 12 months, children in the intervention groups can visit the website, to obtain new information or receive new advice as often as they want.

Six times a year participants in the intervention + prompt condition will be pro-actively prompted through e-mail and SMS to revisit the ‘Fun without Smokes’ website. The first three prompts will be sent 1, 2 and 3 months after the baseline measurement. The last three prompts will be sent 5, 7 and 9 months after baseline. In accordance with the prompts, some of the content of the website will be refreshed to address a new topic relevant for smoking prevention. This procedure will be repeated in the second year of the evaluation study. Participants in the intervention condition will not receive these messages, but will be able to revisit the website whenever they want during the 2-year follow-up period to view the same information as shown to participants in the intervention + prompt condition. The participants in the control condition will not have access to the ‘Fun without Smokes’ website.

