*Smoking Behaviour* will be assessed by self-reports with the question: ‘Which statement describes your behaviour best?’ An internationally accepted algorithm [9,11,43,44] will be used as answering scale, ranking the following items: ‘I have never smoked, not even a puff’, ‘I have tried smoking once, but I do not smoke anymore’, ‘I have quit smoking, I have always smoked less than once a week’, ‘I have quit smoking after having smoked at least once a week’, ‘I try smoking once in a while’, ‘I smoke less than once a month’, ‘I do not smoke weekly, but at least once a month’, ‘I do not smoke daily, but at least once a week’ and ‘I smoke at least once a day’. Children will be categorised as non-smokers (never smoked a puff; have tried smoking, but not anymore; stopped smoking, after smoking less than once a week; stopped smoking, after smoking at least once a week) or as smokers (try smoking sometimes; smoke less than once a month; smoke at least once a month; smoke at least once a week; smoke every day). Smoking during the last 24 hours (‘Have you smoked during the last 24 hours?’), the past 7 days (‘Have you smoked during the past 7 days?’) and during the past month (‘Have you smoked during the past month?’) will be assessed as well. These questions will be assessed with a ‘yes/no’ answering scale. Additionally, a qualitative assessment will be made of the number of cigarettes smoked during the past week and weekend (‘How many cigarettes have you smoked during the last week/weekend?’).

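### The self-reported primary outcome also triggers personal feedback, in the intervention arms only, and a confidentiality promise made equally to all pupils does not address under-reporting that differs by arm

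*Protocol article*

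**What the plan says.** - Objectives and design: "Ever smoking is chosen as the primary outcome measure". Control pupils receive no information.
- Questionnaire: smoking behaviour "will be assessed by self-reports with the question" of which statement fits the pupil best. The lowest answer is "I have never smoked, not even a puff". No objective check is described.
- Procedure: the baseline questionnaire is the instrument "which is also the screening instrument for the tailored feedback messages". Baseline and 12 months are completed at school with a teacher supervising, and 24 months at home.
- Procedure, on who gets feedback, for the baseline and 12-month waves: "the children in the intervention groups will receive short summaries of the tailored feedback on their computer screen". Fuller letters follow by e-mail and on the website. Controls have no access to the website.
- Content of the tailored feedback letters: the determinants addressed include behaviour.
- Intervention framework and procedures, in the text after Figure 1: "All participants will be invited to complete the full assessment questionnaire again 12 and 24 months after the baseline questionnaire is completed, to receive repeated". What is to be received there is letters on changes in smoking status or key determinants. The advice uses answers from previous waves.
- Strengths and limitations: self-report may bring socially desirable answers, and the remedy is "To avoid social desirable answers, we will guarantee full confidentiality to our participants". Possible differences between arms are not mentioned.

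**The concern.** From baseline onwards, pupils in the intervention arms learn that what they enter comes back to them as a personal anti-smoking message. Control pupils have no such experience. If this makes intervention pupils who have smoked less willing to say so at follow-up, their observed ever-smoking rate falls and the programme appears to work. The error runs in the hypothesised direction and falls on the primary outcome. A confidentiality promise that is identical in all arms may reduce under-reporting overall, but it does not address a difference between arms that comes from the feedback itself. A second problem is that the protocol is inconsistent on whether the final outcome wave is itself tied to a letter, and for whom.

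**Working it through.** **Planned comparison.** The inputs come from Sample size calculation and Strengths and limitations: 24% (control), 15% (intervention) and 8% (intervention + prompt); two-sided 0.05; power 0.80; ICC 0.04; 81 schools; 3,240 pupils; 60% drop-out. This gives 3,240/81 = 40 pupils per school and 40 × 0.4 = 16 completers. With equal allocation (assumed) there are 81/3 = 27 schools per arm.

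On the logit scale the variance of the log odds ratio is [(1/(p₁q₁) + 1/(p₂q₂))/m + 2τ]/J, with τ = 0.04/0.96 × π²/3 = 0.137, m completers per school, J schools per arm and a noncentral t on 2J − 2 degrees of freedom. With m = 16, the smallest J reaching 80% power is 27, both for 24% v 15% (power 0.805) and for 15% v 8% (0.811). So the stated 81 schools and 3,240 pupils reproduce exactly. Nothing is wrong with that figure, and it gives a sound base for the illustration.

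**Under-reporting in one intervention arm only.** Assume no true effect, 24% ever smokers in both arms and honest controls. A fraction u of ever smokers in the intervention arm deny it, so the observed rate is 0.24 × (1 − u). The last column uses the formula above with J = 27 and m = 16.

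| u | Observed, intervention v control | Odds ratio | Chance of a significant false benefit |
|---|---|---|---|
| 10% | 21.6% v 24% | 0.87 | 0.10 |
| 20% | 19.2% v 24% | 0.75 | 0.30 |
| 30% | 16.8% v 24% | 0.64 | 0.60 |
| 37.5% | 15.0% v 24% | 0.56 | 0.805 |

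For u = 20%: (0.192/0.808)/(0.24/0.76) = 0.2376/0.3158 = 0.75. If 5% of control ever smokers also deny, the rates are 22.8% v 19.2% and the odds ratio is 0.2376/0.2953 = 0.80.

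**Equal under-reporting.** If 25% deny in both arms, a true 24% v 15% is observed as 18% v 11.25%, a difference of 6.75 points instead of 9. This shrinks a real effect and does not create one.

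**What repeated answers can reveal.** Ever smoking cannot be undone, so an earlier report followed by never is a visible inconsistency. The Background gives 12% at age 12 and double that at 13. On those rates, about 0.12 × 27 × 16 = 52 of the 432 completers per arm could have reported by 12 months. Fewer than that would have reported at baseline. The check is therefore possible but imprecise.

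**The two sections on feedback.**

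| | Text after Figure 1 | Procedure |
|---|---|---|
| Who | all participants | intervention groups |
| Waves | 12 and 24 months | baseline and 12 months |

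They differ on both counts.

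**The case against.** A reader might infer that the confidentiality promise itself differs by arm, or that admitting smoking is what brings a letter. The documents support neither. The promise is made to all participants, log-in details are handed out sealed in every arm, and letters go to the pupil's own e-mail and to pages behind a password. Automated feedback to the pupil is not disclosure to others. Every intervention pupil receives three letters whatever they answer, so denial avoids none. No example in Table 1 repeats an admission of having smoked, although smoking status and behaviour are named elsewhere as feedback content.

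The classroom screen is also a limited mechanism. On-screen summaries are stated for the school waves, whereas the 24-month questionnaire, on which the sample size rests, is completed at home. Baseline answers precede any feedback. At 24 months, learned expectation and the programme's own messages remain.

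It is also tempting to say that the plan would count a pupil who recants as a never smoker. The article does not say how reports are combined across waves, and it may leave that to a fuller document, so this is no fault of the plan. Nor do the documents give any denial rate, and feedback triggered by assessment is inherent in computer tailoring. The authors do acknowledge self-report error in general.

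All of this stands and narrows the point. It leaves two things untouched: the consequence of answering differs by arm, and the stated remedy does not address that difference. On the two sections, the no-information control condition suggests that the reference to all participants is loose wording. Whether a letter follows the 24-month questionnaire remains open.

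**Conclusion.** The point holds in a limited form. The instrument for the primary outcome also triggers personal feedback on smoking-related answers in the intervention arms only, and the uniform confidentiality promise does not address under-reporting that is greater in those arms. Such under-reporting would favour the programme. Its size is unknown: the range runs from little consequence (10% denial, about a 10% chance of a false significant benefit) to the whole planned 24% v 15% contrast (37.5% denial). These figures assume no true effect, honest controls, equal allocation, 16 completers per school and the protocol's ICC. They show sensitivity and are not evidence that the bias exists. The inconsistency between the text after Figure 1 and Procedure is a matter of text and needs no assumption.

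**What to change.** 1. Report by arm the share of pupils who reported having smoked at an earlier wave and later answer "I have never smoked, not even a puff", chiefly among baseline reporters, whose answers precede any feedback. Add a sensitivity analysis among 24-month responders in which ever smoking means any report at any wave. State that both checks miss pupils who deny consistently, and that 12-month reports may themselves be affected.
2. Use identical wording in all arms before the 24-month smoking item, saying that these answers will not be fed back, and run the item so that this is true.
3. Reconcile the text after Figure 1 with Procedure on which arms and waves receive letters, and name arm-dependent reporting as a limitation under Strengths and limitations.

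The cost is one small table and one sensitivity analysis from data already collected, plus a short text at the final wave. There are two downsides. Mistaken earlier reports become permanent under the any-report definition, and any final-wave letter has to be separated from the outcome items.
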